**Figure 3 F3:**
[figure not shown]
Sample sizes in the randomised and patient preference cohort.

#### Uniform preoperative counselling

Uniform counselling is crucial in the RPPT design.^20^ All patients eligible for inclusion in the study will be counselled using the *Patients’ Expectations and Goals of reconstruction. Assisting Shared Understanding of Surgery (PEGASUS*) tool^30 31^ to decide whether they want a breast reconstruction. The tool forms a basis for a patient-centred dialogue around breast reconstruction. An implementation study using PEGASUS in a Swedish context is currently being performed in our department. Following the PEGASUS session, an appointment with a plastic surgeon skilled in both implant-based and autologous breast reconstruction will be scheduled for more technical counselling regarding the two reconstructive options. The information will be standardised for the study.

### Interventions

#### Mastectomy

The mastectomies will be performed by general surgeons (breast surgeons). In case of an immediate breast reconstruction, a skin-sparing mastectomy will be performed. The nipple-areolar complex (NAC) will be preserved if it is oncologically safe. In case of an immediate breast reconstruction, a Wise pattern skin resection will be made in ptotic; otherwise, a submammary incision, or vertical incision if the NAC has to be removed, will be performed. Delayed breast reconstruction will be performed following a simple mastectomy. All reconstructions will be performed by consultant plastic surgeons with a subspecialty in breast reconstruction and a minimum of 5 years of independent experience with the used techniques.

#### Autologous breast reconstruction: DIEP-flap

All DIEP-flaps are performed by plastic surgeons according to the standard of care of the department. In summary, it is performed as a cutaneous-adipose flap, without muscle, and if possible anastomosed to the internal thoracic artery and vein. If needed, the superficial epigastric vein is anastomosed to the cephalic vein through a small incision in the axillary fold. If possible, the flap is buried, when an immediate breast reconstruction is performed. In delayed breast reconstruction, a skin island is inserted between the submammary fold and the old mastectomy scar.

#### Implant-based breast reconstruction

All implant-based breast reconstructions are performed by plastic surgeons according to the standard of care of the department. In immediate breast reconstruction, a subpectoral pocket is created, and the inferior-medial and inferior attachments of the major pectoral muscle are released. If a permanent implant (CPG, Mentor Worldwide LLC, California, USA) is used, a synthetic TIGR Matrix Surgical Mesh (Novus Scientific, Uppsala, Sweden)^32 33^ is sutured to the inferior border of the pectoral muscle and to the chest wall corresponding to the inframammary fold and lateral border of the implant pocket; hence, a dual plane approach is applied. *The Gothenburg TIGR/Veritas Study*^33^,^35^ comparing a biological and a synthetic mesh in immediate breast reconstruction demonstrated that the synthetic mesh is superior to the biological regarding complications and is equivalent regarding patient satisfaction. Therefore, the synthetic mesh has become a standard of care and will be used in the present study. If a tissue expander (CPX4 or Siltex Becker, Mentor Worldwide LLC) is used, a m. serratus pocket is created to block the expander laterally to achieve a muscle-covered device. A temporary expander is exchanged for a permanent implant about 3 months after the initial operation.

### Criteria for discontinuing or modifying allocated interventions for a given trial participant

Trial participants have the right to withdraw from the study at any time without any consequence. Before the reconstruction, patients can change from the randomised cohort to the preference cohort should they change their wishes. Their data will then be analysed according to their change. If the patient regrets her choice of cohort after her reconstruction, she will be included in the analysis of her original cohort, but her change of preference will be noted.

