Randomised controlled trials (RCT) are generally thought to provide the most solid scientific evidence for treatment effects. However, there are barriers to conducting RCTs in breast reconstruction, making both recruitment and achieving unbiased and generalisable results a challenge.^9 10^ First, an RCT requires that there is solid uncertainty about which method achieves the best results. In the case of breast reconstruction, the operating surgeon must not prefer one method to another (*theoretical equipoise*)^11^ as this could result in both biased recruitment as well as biased outcomes if the included patients receive biased preoperative and postoperative information.^9^ The patient must also not have preformed ideas and clear preferences regarding the different methods (*principle of indifference*)^11^ based on, for example, other patients, patient organisations, and the media, as this also affects the recruitment and the results. Patients’ preferences can affect the external validity if a standard treatment, for example, implant-based breast reconstruction in non-irradiated patients,^12^ is compared with an alternative treatment, for example, autologous reconstruction, as only patients who prefer autologous reconstruction are likely to accept randomisation. Patients’ preferences could also reduce internal validity as randomisation to the (non-) preferred strategy could affect both adherence to the protocol (*reluctant acquiescence phenomenon*)^13^ and outcome. All these factors would lead to results that are not generalisable to the clinical population. This risk of bias and low internal and external validity illustrates why an RCT can be an inappropriate study design when comparing different categories of breast reconstruction.

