A PubMed search on breast AND reconstruction, limited to RCTs, yields 419 results (10.07.2023).^14^ One-hundred and nine of them are RCTs concerning some aspect of breast reconstruction. The majority compared surgical variation within the same category of breast reconstruction technique, for example, one versus two stages or mesh versus no mesh in implant-based breast reconstruction and preoperative imaging versus no preoperative imaging in autologous breast reconstruction. Only four studies compare different categories of breast reconstruction techniques head to head^15^,^18^ and they all illustrate the aforementioned challenges with RCTs in breast reconstruction. For example, in the RCT performed in our department, the Gothenburg Breast Reconstitution trial (GoBreast),^18 19^ preintervention dropouts rates after randomisation varied between 12.5% and 23% in different groups, due to either the patient’s or surgeon’s preferences.

The study design partially randomised patient preference trial (RPPT) is an approach to diminish the impact of patients’ preferences, facilitate recruitment, increase patient centricity, decrease the risk of excluding large patient groups and make the results more generalisable to the clinical population, when preference-sensitive interventions are compared.^20^ In an RPPT, patients with a clear preference are treated accordingly and patients without a distinct preference are randomised in the traditional way. The RPPT design enables a more efficient inclusion of participants, and a clinically more representative study population, while maintaining a high external and internal validity.^20^ GoBreast II will mark the first use of an RPPT design to evaluate breast reconstruction methods.

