### Randomised patients and randomisation processes

Participants that accept randomisation will be randomised in a 1:1 ratio, using simple randomisation, with equal probability, to either autologous or implant-based reconstruction (figure 3). The mechanism of implementing the allocation sequence is sealed envelope. Allocation sequence will be ensured as the sequence will be concealed for participants, surgeons and research staff until the participant has been included in the randomised arm, which takes place after all inclusion and exclusion criteria have been checked, the PEGASUS intervention performed, and baseline clinical evaluation completed at the appointment with the plastic surgeon. All patients giving consent to participate in the randomised cohort that fulfils inclusion criteria will be randomised. Randomisation will be conducted without any influence from the surgeons/researchers. The intervention nature does not allow blinding.

In the patient preference cohort, patients will be included until the minimum targeted sample size has been reached, that is, until the minimum number of participants has selected the least popular alternative (figure 3).

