### Statistical methods

A detailed statistical analysis plan will be drafted early in the trial and finalised before primary outcome analysis. All analysis will be performed on an intention-to-treat basis and per-protocol analysis as sensitivity analysis. Descriptive data will be given as appropriate according to type of data and if it is skewed or not. This will also form the basis for statistical tests chosen to compare groups. Sensitivity analysis will be done were missing data in predictors will be handled by multiple imputation methods.^50^ Regression analysis preceded by collinearity check of potential predictors and performed to allow for correction for possible confounders. Residuals for each regression analysis will be checked for the assumptions of normal distribution and constant deviation along the predicted values. Subgroup analyses will be performed for the randomised and the preference cohort and for timing of reconstruction (immediate/delayed reconstruction) and for patients who unexpectedly will require radiotherapy. The statistical analysis will adhere to the Setting Intenartional Standards in Analysing Patient-Reported Outcomes and Quality of Life Endpoints in Cancer Clinical Trials (SISOQOL) framework.^51^ All tests will be two tailed and a p value of ≤0.05 will be considered to indicate a statistical significance.

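### Randomised women who change cohort before surgery are analysed by the change, even once their allocation is known; this contradicts the promised intention-to-treat analysis

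*Protocol article*

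**What the plan says.** The section on criteria for discontinuing or modifying allocated interventions gives two rules. Before surgery: "Before the reconstruction, patients can change from the randomised cohort to the preference cohort should they change their wishes", followed by "Their data will then be analysed according to their change". After surgery, a woman who regrets her choice is treated the other way: "she will be included in the analysis of her original cohort, but her change of preference will be noted".

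The Statistical methods section states one principle for everything: "All analysis will be performed on an intention-to-treat basis and per-protocol analysis as sensitivity analysis".

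The section on randomisation processes says that "the sequence will be concealed for participants, surgeons and research staff until the participant has been included in the randomised arm", and adds that the nature of the intervention rules out blinding.

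The Background reports that in the department's earlier randomised trial "preintervention dropouts rates after randomisation varied between 12.5% and 23% in different groups", owing to patient or surgeon preference.

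**The concern.** Take a woman who consents to randomisation, learns her arm and then changes her mind before the operation. Intention-to-treat keeps her in the randomised cohort, in the arm she was given. The pre-surgery rule takes her out of that cohort and analyses her with the women who chose. Both instructions cannot be followed for the same woman.

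The choice between them matters because leaving is self-selected and can depend on which arm was drawn. If it does, and if those who leave would have scored differently from those who stay, the remaining arms are no longer the groups that randomisation formed. The switchers also enter the preference cohort, so the planned comparison of the two cohorts is affected as well.

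**Working it through.** **1. Does the rule reach women who know their allocation?** The window for moving runs to the reconstruction. Concealment ends at inclusion in the randomised arm, which comes earlier. The rule therefore covers the interval between the two, and no other section restricts it to the time before the envelope is opened.

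**2. The plan's own sample size.** Inputs from the Sample size section: difference 10, SD 18, power 0.80, alpha 0.05 (two-sided, from Statistical methods), 20% dropout, 62 per arm.

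- n = 2 × (1.960 + 0.842)² × 18² / 10² = 50.9, so 51 per arm.
- 51 × 1.2 = 61.2, so 62, as stated. Dividing by 0.8 instead gives 64. The gap is small and is not the point here.
- 62 × 0.8 = 49.6 analysed per arm gives power of about 78% (t distribution; 79% by the normal approximation).

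**3. Bias under the current rule (illustration).** Let a share s of an arm switch, and let switchers score g points below stayers. The stayers' mean then lies s × g above the mean of the full arm, so with arm shares s₁ and s₂ the bias is g × (s₁ − s₂). Type I error is the chance that a two-sided 5% t-test rejects when the true effect is zero, with noncentrality bias/SE and SE = 18 × √(1/n₁ + 1/n₂). The shares 12.5% and 23% are borrowed from the earlier trial; g = 10 and the 0% arm are assumptions.

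| Switching | Bias | n per arm, no other loss | Type I error | n per arm, 20% further loss | Type I error |
|---|---|---|---|---|---|
| 23% / 12.5% | 10 × 0.105 = 1.05 | 47.7 / 54.3 | 6.0% | 38.2 / 43.4 | 5.8% |
| 23% / 0% | 10 × 0.23 = 2.3 | 47.7 / 62 | 10.1% | 38.2 / 49.6 | 9.0% |
| 12.5% / 12.5%, similar women | 0 | 54.3 / 54.3 | 5.0% | 43.4 / 43.4 | 5.0% |

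The formula assumes that switchers from both arms differ from stayers in the same direction. If the directions were opposite, the two terms would add: 10 × (0.23 + 0.125) = 3.55 points. The protocol does not indicate which holds.

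**4. Power under the current rule, for 10 points.**

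- Switching on top of 20% dropout: 62 × 0.875 × 0.8 = 43.4 per arm, power 73%; 62 × 0.77 × 0.8 = 38.2 per arm, power 67%.
- Switching as the only loss: 54.3 per arm, 82%; 47.7 per arm, 77%.

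**5. Power if intention-to-treat is kept.** Assume switchers receive the other procedure and the full 10 points follows the procedure received.

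- 12.5% and 23% crossing over: 10 × (1 − 0.125 − 0.23) = 6.45 points; power about 42% at 49.6 per arm. Restoring 80% would take 2 × (2.802)² × 18² / 6.45², about 122 analysed per arm.
- 23% and 0%: 7.7 points; power about 56%; about 86 analysed per arm for 80%.

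**The case against.** Four counter-arguments deserve weight.

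- **The wording does not say after randomisation.** A change between consent and opening the envelope would do no harm. That is true, but the text runs to surgery without limit, and its heading speaks of allocated interventions.
- **A reader might infer that the protocol itself expects women to accept randomisation hoping for a flap and to leave when allocated an implant.** It does not say so. The remark that "only patients who prefer autologous reconstruction are likely to accept randomisation" concerns external validity in a conventional trial, and who accepts randomisation rather than who leaves afterwards. In this design a woman who wants one method can choose it outright, which weakens the incentive to switch.
- **The 12.5–23% is not a forecast.** It comes from a trial with no preference cohort that compared other techniques, and it includes losses due to surgeons' preferences. Switching here could be lower, or higher because it is openly offered.
- **The power loss is partly assumed.** The Sample size section does not say whether its 20% already includes losses before surgery. If switching is the only loss, power stays close to plan.

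All of this limits the size of the problem. None of it removes the conflict between the two rules. A later analysis plan does not cure it either: the protocol states the rule itself, so a plan must break one of the two statements. The per-protocol sensitivity analysis does not help, because the rule alters the main analysis set.

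**Conclusion.** The point holds as a contradiction between two stated rules. As written, the pre-surgery rule overrides intention-to-treat for women who already know their arm and opens the randomised comparison to selection that depends on allocation and preference.

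The size cannot be fixed from the document. It is about zero if both arms lose the same share of similar women. With a 10-point gap in the same direction in both arms, it is about 1 point at 23% against 12.5% and about 2.3 points at 23% against 0%, set against a target difference of 10. These figures rest on borrowed switching rates and an assumed gap. A reader might conclude that the trial's only unbiased comparison is destroyed; the document does not support that. The comparison is weakened in proportion to differential switching, which is unknown.

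**What to change.** Replace the analysis sentence with wording to this effect: once the allocation has been revealed, a participant is analysed in the randomised cohort and in her allocated arm for the primary intention-to-treat comparison, whatever reconstruction she receives; the switch and its reason are recorded, and questionnaires continue. Allow an analytic change of cohort only before the envelope is opened. Report analyses by changed cohort, as-treated or complier-average as sensitivity analyses. Women's freedom to choose their treatment stays as it is.

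The text change is one paragraph, best made before outcome data are seen. It is not free in power: crossover dilutes the intention-to-treat contrast, and at 12.5% and 23% the loss is larger than under the current rule (about 42% against 67–73%, on the assumptions above). The Sample size section should therefore qualify the 80% for the expected share of switchers, and the sponsor should decide whether 62 per arm is still enough.

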### Concomitant care and follow-up visits

Treatment of the patients will be conducted by standard of care regardless of trial participation. Routine clinical assessment will be performed in accordance with the standard of care. No extra trial-specific clinical follow-up assessments will be performed.

### Randomised patients and randomisation processes

Participants that accept randomisation will be randomised in a 1:1 ratio, using simple randomisation, with equal probability, to either autologous or implant-based reconstruction (figure 3). The mechanism of implementing the allocation sequence is sealed envelope. Allocation sequence will be ensured as the sequence will be concealed for participants, surgeons and research staff until the participant has been included in the randomised arm, which takes place after all inclusion and exclusion criteria have been checked, the PEGASUS intervention performed, and baseline clinical evaluation completed at the appointment with the plastic surgeon. All patients giving consent to participate in the randomised cohort that fulfils inclusion criteria will be randomised. Randomisation will be conducted without any influence from the surgeons/researchers. The intervention nature does not allow blinding.

In the patient preference cohort, patients will be included until the minimum targeted sample size has been reached, that is, until the minimum number of participants has selected the least popular alternative (figure 3).

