#### Sample size

The study is s a superiority trial based on the BREAST-Q domain *Satisfaction with the breast/s*.^25^,^27^ The clinically meaningful difference in BREAST-Q was set to 10 points. There are no anchor-based minimal important differences (MIDs) published for BREAST-Q, but the distribution-based MID is 4 for satisfaction with the breast/s.^28^ The SD was set to 18, as calculated according to US norms.^29^ If power is set to 0.80 and alpha to 0.05, the case-to-control ratio is 1, and a 20% dropout rate is expected, 62 patients are needed in each group (https://riskcalc.org/samplesize/). In the randomised cohort, 124 participants will be randomised 1:1. In the preference cohort, patients will be included until 62 participants have selected the least popular alternative (figure 3). This will result in an overall trial cohort with a minimum of 124 participants in each arm and enough participants in the subgroups *randomised* and *patient preference* to allow for analyses of differences.

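### The protocol states a minimum of 124 participants per arm as certain, but simple randomisation of a fixed 124 does not guarantee it

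*Protocol article*

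**What the plan says.** The Sample size section of the protocol article states that "62 patients are needed in each group". It fixes the randomised cohort at 124 patients, allocated 1:1. The preference cohort stays open until the less chosen method has 62 patients, so the other method has at least 62. From this the section concludes: "This will result in an overall trial cohort with a minimum of 124 participants in each arm".

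The section on randomised patients and randomisation processes fixes the allocation method: patients are allocated "using simple randomisation, with equal probability, to either autologous or implant-based reconstruction", by sealed envelope. It names no block and no stratum. The preference cohort has a stopping rule tied to its smaller arm; the randomised cohort has none.

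Two other sections bear on the point. Statistical methods plans a subgroup analysis by immediate versus delayed reconstruction, and regression to correct for possible confounders. The section on discontinuing or modifying allocated interventions lets a randomised patient move to the preference cohort before surgery and be analysed accordingly.

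**The concern.** The stated minimum is 62 randomised plus 62 preference patients per arm. The second 62 is secured by a stopping rule. The first is not: when each of 124 patients is allocated by an independent coin toss, the arm size is a random variable with mean 62. The protocol therefore reports as certain a property that its allocation method does not have. Both statements are explicit in the text, so the mismatch does not depend on an unseen analysis plan.

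The same choice leaves timing of reconstruction to chance. The Interventions section shows that timing changes the mastectomy, the flap inset and the implant technique, and the protocol singles it out for subgroup analysis. A chance difference between arms in the share of immediate reconstructions would add some avoidable noise to the unadjusted primary comparison.

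**Working it through.** **Inputs from the Sample size and Statistical methods sections.** Difference 10 points ("The clinically meaningful difference in BREAST-Q was set to 10 points"), SD 18 ("The SD was set to 18, as calculated according to US norms"), power 0.80, alpha 0.05, ratio 1 and 20% dropout ("If power is set to 0.80 and alpha to 0.05, the case-to-control ratio is 1, and a 20% dropout rate is expected"), two-sided tests, 124 randomised.

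**1. The plan's own figure.** n per arm = 2 × [18 × (1.960 + 0.842) / 10]² = 50.9, rounded up to 51. Adding 20% gives 51 × 1.2 = 61.2, rounded up to 62, which reproduces the stated number. Dividing by 0.8 instead gives 63.75, rounded up to 64. That is a separate matter, and it is why power after 20% loss starts at 79.0% rather than 80% below.

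**2. Randomised arm sizes.** Let X be the number allocated to one arm, X ~ Binomial(124, 0.5).
- P(X = 62) = C(124, 62) / 2^124 = 0.0715. One randomised arm is below 62 with probability 1 − 0.0715 = 92.8%.
- SD of X = √124 / 2 = 5.6; 95% range 51 to 73.
- Mean absolute difference between arms = 8.87, so the expected smaller arm = (124 − 8.87) / 2 = 57.6.
- P(smaller arm ≤ 57) = 42%; P(≤ 52) = 8.8%; P(≤ 51) = 5.9%.

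**3. The overall minimum of 124 per arm.** The less popular method has exactly 62 preference patients; the more popular has 62 + e. Let X be the randomised number in the less popular method. Some arm misses 124 if X < 62, or if (124 − X) + 62 + e < 124, that is X > 62 + e. So P(miss) = P(X < 62) + P(X > 62 + e), where P(X < 62) = (1 − 0.0715) / 2 = 0.464. The protocol text does not give e, so a range is assumed:

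| Surplus e | P(X < 62) | P(X > 62 + e) | P(miss) |
|---|---|---|---|
| 0 | 0.464 | 0.464 | 93% |
| 5 | 0.464 | 0.162 | 63% |
| 10 | 0.464 | 0.029 | 49% |
| 20 | 0.464 | <0.001 | 46% |

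The floor is 46%: nothing offsets a randomised shortfall in the less popular method. All figures are before any cohort switching.

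**4. Power.** Normal approximation, each arm reduced by 20%: power = Φ(10 / [18 √(1/n1 + 1/n2)] − 1.96).
- 62/62 becomes 49.6/49.6: SE 3.614, Φ(2.767 − 1.96) = 79.0%.
- 51/73 becomes 40.8/58.4: SE 3.673, Φ(2.723 − 1.96) = 77.7%.
- Averaged over all binomial splits: 78.7%.

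**5. Timing.** The share p of immediate reconstructions is not given, so 20% to 50% is assumed. With 62 per arm, the SD of the difference in share is √[p(1 − p) × 2/62].

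| p | SD | P(gap > 10 points) | P(gap > 20 points) |
|---|---|---|---|
| 0.2 | 0.072 | 16% | 0.5% |
| 0.3 | 0.082 | 22% | 1.5% |
| 0.5 | 0.090 | 27% | 2.6% |

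**6. What blocking would achieve.** With block sizes of 4 and 6 (an example) and two strata, an unfinished block leaves the arms at most 3 apart in each stratum, so at most 6 apart in all. The smaller arm is then at least (124 − 6) / 2 = 59.

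**The case against.** The strongest defence is that simple randomisation is valid, unbiased and fully unpredictable. That matters in an unblinded, single-centre trial using sealed envelopes, whose Introduction reports dropout of 12.5% to 23% after randomisation in the predecessor trial because of patient or surgeon preference. Blocks give up some of that unpredictability for about 0.3 points of average power (79.0% against 78.7%). This stands, and it makes blocking an option rather than a necessity.

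Three stronger readings are tempting, and the document does not support them.
- A reader might infer that the 124 minimum fails in 93% of trials. That figure describes the randomised arms alone, or the overall cohort with no preference surplus. A surplus in the more popular method can absorb a shortfall there, which lowers the chance of a miss to as little as 46%. The minimum is not guaranteed; it is not certain to fail.
- A reader might infer that timing will be unbalanced. Simple randomisation balances it in expectation, gaps above 20 points are uncommon, and Statistical methods allows regression adjustment. A subgroup analysis compares the methods within each timing group, so unequal shares between arms do not bias it.
- A reader might infer that the trial loses material power. The loss is about one point at the edge of the 95% range.

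It is also fair to say that a blocked list does not by itself secure 62 analysed patients per arm, because randomised patients may change cohort before surgery. Figure 3, which covers sample sizes, is not shown, but the two statements in the text conflict without it.

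**Conclusion.** The point holds as an inconsistency between the stated arm sizes and the stated allocation method. The minimum of 124 per arm is presented as an outcome of the design, yet it is missed with probability 46% to 93%, depending on a preference surplus that the text does not fix. Exactly 62/62 occurs with probability 7.2%. These figures assume that 124 patients are randomised with equal probability and that no one switches cohort.

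The practical consequence is modest. Power moves from 79.0% to 77.7% at 51/73, and the validity of the randomised comparison is not in question. Timing of reconstruction is uncontrolled in the allocation rather than unbalanced; the probabilities for it rest on an assumed share of 20% to 50% immediate reconstructions. The sentence on arm sizes is wrong as written and should be corrected. Changing the randomisation method is a reasonable choice on which statisticians may differ.

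**What to change.** Either of two changes resolves the inconsistency.

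- **Keep simple randomisation.** In the Sample size section, call 62 per randomised arm and 124 per arm overall expected numbers, and delete the word minimum. The cost is a wording change.
- **Change the allocation.** Use permuted blocks of randomly varying size, withheld from surgeons and research staff, stratified by immediate versus delayed reconstruction, with the stratum in the primary model. This holds the allocated arms at or within a few patients of 62. Describe 124 per arm as the approximate allocated number before cohort switching, since neither unfinished blocks nor switching allows a strict minimum. The cost is a new allocation list and a short amendment; the downside is slight predictability in an unblinded single-centre trial, limited by varying and concealing the block sizes.

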### Trial design

GoBreast II is a partially RPPT with a superiority framework. Participants who accept randomisation will be allocated to one of the two methods. Participants who do not accept randomisation will be operated with their preferred method. Thus, the study has two cohorts: one randomised and one patient preference (figure 1). The trial is a single-centre study conducted at a university hospital in Sweden. It has embedded qualitative and health economic research questions.

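### Sealed envelopes are the only named allocation mechanism in this open, single-centre preference trial; locked central allocation would protect concealment better at small cost

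*Protocol article*

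**What the plan says.** All places are in the protocol article.

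- **Mechanism** (Randomised patients and randomisation processes): "The mechanism of implementing the allocation sequence is sealed envelope". I read this as physical envelopes. The article does not say who prepares, holds or opens them.
- **Sequence** (same section): women are "randomised in a 1:1 ratio, using simple randomisation, with equal probability".
- **Concealment and independence** (same section): "the sequence will be concealed for participants, surgeons and research staff until the participant has been included in the randomised arm", and "Randomisation will be conducted without any influence from the surgeons/researchers". Entry to the randomised arm follows the eligibility check, the counselling tool and the baseline evaluation. Consent or assent adds that written consent precedes allocation.
- **Who is randomised** (same section): "All patients giving consent to participate in the randomised cohort that fulfils inclusion criteria will be randomised".
- **Blinding** (same section): "The intervention nature does not allow blinding".
- **The other way in** (Trial design): "Participants who do not accept randomisation will be operated with their preferred method". The same section says the trial is single-centre.
- **Experience in the same department** (Background and rationale): in the predecessor trial, "preintervention dropouts rates after randomisation varied between 12.5% and 23% in different groups, due to either the patient’s or surgeon’s preferences".
- **Switching** (Criteria for discontinuing or modifying allocated interventions): until the reconstruction a woman may move from the randomised to the preference cohort, and her data then follow the move. Noting a change is stated only for regret after the reconstruction.
- **Analysis** (Statistical methods): every analysis is by intention to treat, with per-protocol as sensitivity analysis.

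**The concern.** The randomised cohort is the only part of this trial free of confounding by preference, and its value depends on nobody knowing the next allocation when a woman is assigned to a cohort. The article asserts that outcome. The mechanism it names relies on how the envelopes are handled, and it describes no independent record, made before the draw, of who was entered and into which cohort.

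Three features make this matter more here than in an ordinary surgical trial:

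- The treatments are open and the primary outcome is patient-reported.
- Preferences are strong. The article itself warns that surgeon preference can bias recruitment, and it states a hypothesis favouring the autologous method. It also notes that theatre capacity allows one autologous reconstruction a day against three implant-based ones.
- A woman who does not enter the randomised cohort need not leave the trial. She can join the preference cohort and have the operation she prefers. In a conventional trial the same decision would appear as a refusal.

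If some draws were foreseen and influenced who entered the randomised cohort, the randomised difference in satisfaction with the breasts would be biased.

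**Working it through.** **1. The plan's own figure.** From Sample size: difference 10, SD 18, two-sided alpha 0.05, power 0.80. Then n = 2 × (18 × (1.960 + 0.842) / 10)² = 50.9, so 51 per group. Adding 20% gives 51 × 1.2 = 61.2, so 62, as stated. (Dividing by 0.8 gives 64.) The sample size does not bear on this point; it supplies the standard error.

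**2. Standard error.** With 62 per arm and 20% loss, 62 × 0.8 = 49.6 are evaluable. SE = 18 × √(2/49.6) = 3.61 points.

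**3. Steering before the draw.** Assumptions that are not in the documents:

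- a share f of draws is foreseen;
- for a foreseen draw, only women on one side of the median of some trait are entered;
- that trait correlates r = 0.3 with the outcome.

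The mean of a half-normal variable is √(2/π) = 0.80 SD, so

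bias = k × f × r × 18 × √(2/π) = k × f × 4.31 points,

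with k = 1 if only draws for one arm are exploited and k = 2 if both are, in opposite directions. The false-positive rate is the two-sided 5% rejection probability at bias/SE.

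| Share foreseen | Bias, one arm | Bias, both arms | False-positive rate, one arm | False-positive rate, both arms |
|---|---|---|---|---|
| 10% | 0.43 | 0.86 | 5.2% | 5.7% |
| 20% | 0.86 | 1.72 | 5.7% | 7.6% |
| 50% | 2.15 | 4.31 | 9.2% | 22.2% |

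A simulation of 124 women under simple randomisation with 20% loss agrees: 5.3, 6.0 and 9.6% (one arm), and 5.5, 7.7 and 22.0% (both arms). For scale, Sample size gives a target of 10 points and a distribution-based minimal important difference of 4. Only the extreme cell, half of all draws foreseen and both arms steered, exceeds 4.

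**4. Would steering show at baseline?** Under the same model the imbalance between arms in the steering trait is k × f × 0.80 SD. Its standard error with 62 per arm is √(2/62) = 0.18 SD.

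- f = 50%: 0.40 to 0.80 SD, z = 2.2 to 4.4. Usually visible, if the trait or a close proxy is measured.
- f = 20%: 0.16 to 0.32 SD, z = 0.9 to 1.8. Often not distinguishable from chance.

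**5. Leaving after the draw, a separate route.** Suppose a share f of an arm moves out after the draw and would have scored g points below the arm mean. The mean of those who stay shifts by f/(1−f) × g. Take f from the predecessor's 12.5% and 23%, and assume g of 4 to 18 points.

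- f = 12.5%: 0.143 × 4 = 0.6 to 0.143 × 18 = 2.6 points (one arm).
- f = 23%: 0.299 × 4 = 1.2 to 0.299 × 18 = 5.4 points (one arm).

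The documents give no value for g, and it is not known whether the predecessor's rates would recur in a design that lets women with clear preferences opt out beforehand. This route is open however the sequence is concealed.

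**The case against.** A reader might infer that staff can inspect or swap the envelopes and so steer the randomised comparison unseen. The documents do not support that. Nothing says the envelopes are kept in the department, can be read through, or are unnumbered or unlogged, and such handling details are commonly left to the full protocol. The article states concealment, puts eligibility, counselling, baseline evaluation and consent before allocation, and says every eligible woman who consents to the randomised cohort is randomised. Simple randomisation without blocks cannot be predicted from past draws. Nor can staff simply enter a woman as a preference participant; she has to decline randomisation herself.

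A second tempting inference is that the predecessor's 12.5-23% shows a risk of breached concealment. Those losses came after randomisation. They show women or surgeons not accepting a known allocation, and the article presents the preference design as the response to that.

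A third is that the final data could never reveal steering. Study within a trial reports the rate accepting randomisation and compares the cohorts on several preoperative measures. Adherence has questionnaires given at allocation, so the arms can be compared as well, and Statistical methods plans regression for confounders. Large steering would usually show.

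All of this stands, and it limits the point. What remains is that envelopes are a stated choice, weaker than an available alternative, and that baseline checks are least sensitive to the smaller amounts of steering.

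**Conclusion.** The point holds as a low-cost improvement to a stated design choice, not as a demonstrated error. Envelopes are the only mechanism named, and the concealment and no-influence statements have no described step behind them beyond the order of events. Central allocation secures both better.

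The size of any bias is unknown. The 0.4-1.7 points for 10-20% of draws foreseen, with a false-positive rate of at most about 8%, rest on an assumed share, an assumed correlation of 0.3 and perfect sorting at the median. Reading the mechanism as physical envelopes is also an assumption.

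The switching rule is a distinct weakness visible in the text. Analysing a woman according to a move made after her draw takes her out of the randomised comparison, which conflicts with intention to treat. A change of allocation mechanism would leave this untouched, so both need attention.

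**What to change.** 1. **Allocation.** In Randomised patients and randomisation processes, replace the envelopes with central or third-party computer allocation, with the list generated and held outside the recruiting team. Release the allocation only after study ID, eligibility, consent and chosen cohort have been entered, locked and time-stamped.
2. **Back-up.** If envelopes are kept as back-up, make them opaque and sequentially numbered, hold them independently of the recruiting team, write ID and date on the outside before opening, and reconcile them with the list.
3. **Switches.** Log every change of cohort with its date, the drawn arm and the reason, including changes before the reconstruction.
4. **Analysis.** Reconcile the switching rule with the intention-to-treat statement so that every randomised woman stays in her drawn arm for the primary randomised comparison. This concerns the analysis set only; it does not restrict her freedom to change.

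The cost is a protocol amendment, a short set-up effort for a standard randomisation module, and dependence on the system being available at the clinic appointment. No extra patients or visits are needed. Concealment cannot be restored for women already enrolled, so early adoption is worth more than late.
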